### Analysis

Our primary hypothesis is that students in schools receiving the intervention will report less violence (over time) compared to students in the control group. We also hypothesize that the intervention schools have an overall lower rate of violence over the school year compared with control schools. We expect that using implementation facilitation led by a climate specialist as part of a 3-person leadership team is a feasible and sustainable approach to integrating and effectively delivering the three intervention components. Finally, we expect that students in the intervention schools will report more positive school climate compared with those in control schools and that this, in turn, will result in lower improved mental health outcomes.

A cluster randomization design is proposed with random assignment by school to one of two arms: intervention or control. Evaluation of effectiveness outcomes will involve testing at four time points: a fall of Year 1, spring of Year 1, fall of Year 2, spring of Year 2. Measures will include school records and self-report data from students and teachers. The survey of students makes use of currently collected MiPHY data. Ten schools will be recruited in the first year and 10 in the following year; staggered recruitment will allow some initial evaluation testing of the program and allow the earliest possible start time with a number of schools. Including 20 schools in the research provides an opportunity to examine school level differences. To adjust for bias introduced by multiple comparisons across our outcome variables, we will use a pair of conservative (Tukey and Bonferonni) *p*-value adjustments in addition to reporting direct effect sizes (e.g., group differences in means) to allow for assessment not dependent on standard null hypothesis testing.

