### Sample

#### Schools

We will recruit 20 schools and implement the intervention across three school years (see Table 1). Co-educational elementary schools in Genesee County Intermediate School District (GISD), Michigan will be invited to participate. Schools participating will be similar in terms of proportion of students receiving free/reduced school lunches and approximate size of the school. Prior to the intervention roll-out, all 20 schools will be randomized to intervention or control. The intervention will be implemented in stages. Cohort 1 schools will include 5 intervention and 5 control schools. Cohort 2 will include10 additional schools (5 intervention and 5 control) for a total of 10 intervention and 10 control schools; each school will implement the intervention for two years.

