#### Restorative justice (RJ)

Restorative justice is a philosophy and process that defines crime as doing harm to people and relationships, rather than simply violating the law (Zehr, 2002). Thus, it requires consideration of the victim and community during the justice process. Although the definition continues to evolve, it has most commonly been described as “a process whereby all the parties with a stake in a particular offense come together to resolve collectively how to deal with the aftermath of the offense and its implications for the future” (Marshall, 1996). Restorative practices focus on repairing the harm caused, engaging victims and relevant school community members in the decision making process, holding offenders accountable, and preventing similar actions in the future. By focusing on accountability, fairness, and situational responses to unique events, restorative justice provides a useful framework for alternatives to zero tolerance or traditional disciplinary actions for school violence. Overall, researchers have found robust support for RJ practices, including enhanced school safety, reduced discipline problems and other behavioral referrals (Karp & Breslin, 2001; Mirsky, 2011; Stinchcomb, Bazemore, & Riestenberg, 2006).

Prior research suggests that RJ practices may have particular efficacy for youth in the age ranges targeted in this project. Researchers found, among students 14 years and younger, that youths participating in family group conferences were less likely to re-offend than youths participating in other court-ordered programs (McGarrell & Hipple, 2007). Further, offending youths, parents, and victims all expressed much more favorable perceptions of the fairness, respect, and value of the conference experience (McGarrell, 2001). Long-term follow-up of this research demonstrated that conferences following principles of “restorativeness” and “procedural fairness” were associated with reduced re-offending at 24 months and 10 years following the original conference (Hipple, Gruenewald, & McGarrell, 2014, 2015).

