### Measures

A summary of the measures is provided in Table 2.

**Table 2 Tab2:** Data sources and measures

Aim	Measures	Measure frequency	Data Sources	Original Data Sources
Primary: Intervention effectiveness on violence outcomes	Aggression, violence victimization, bullying	Fall Year 1, Spring Year 1, Fall Year 2, Spring Year 2	Michigan Profile for Healthy Youth Survey (MiPHY)^a^	Youth Risk Behavior Surveillance Survey (YRBSS)^b^ Bully-Free Schools Survey (BFSS)^c^
	Truancy, behavioral referrals	Spring Year 1, Fall Year 2, Spring Year 2	School Information System (SIS)	School Student Data
Secondary: feasibility and potential utility of implementation facilitation	Meeting agenda, interview prompts	Spring Year 1, Spring Year 2	Staff, student and 3-Person Leadership Team (3-PLT) focus groups	Questions developed by research team
	School climate, perceptions of program effectiveness (e.g., violence)	Spring Year 1, Spring Year 2	Delaware School Climate Teacher/Staff Survey^d^	Delaware School Survey - Teacher/Staff (DSS-T/S)^d^
Secondary: mechanisms and mental health	School climate scale	Fall Year 1, Spring Year 1, Fall Year 2, Spring Year 2	Delaware School Climate Student Survey^d^	Delaware School Survey - Student (DSS-S)^d^
	Anxiety, depressive symptoms, wellbeing	Fall Year 1, Spring Year 1, Fall Year 2, Spring Year 2	Michigan Profile for Healthy Youth Survey (MiPHY)^a^	Youth Risk Behavior Surveillance Survey (YRBSS)^b^
Secondary: Cost-benefit	Intervention (e.g.,materials) and imple-mentation costs (e.g., training, support)	Monthly	Time tracking by research and school staff	Data collected by research team

^a^(Michigan Department of Education, 2016), ^b^ (Kann et al., 2018), ^c^ (Lindenberger, 2005), ^d^ (Bear et al., 2016)

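### Tukey gives no protection across outcomes in a two-arm trial and can contradict the Bonferroni result it is paired with, and the power statement shows no allowance for several primary measures

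*Protocol article*

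**What the plan says.** The Analysis section gives the purpose of the adjustment, "To adjust for bias introduced by multiple comparisons across our outcome variables", and then the method: "we will use a pair of conservative (Tukey and Bonferonni", both applied to the p-values. It adds that effect sizes will be reported so that readers need not depend on significance tests alone. The same section describes "random assignment by school to one of two arms: intervention or control", and the Schools section gives the split "for a total of 10 intervention and 10 control schools".

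In Table 2 (Measures), the primary row lists three student-survey measures, "Aggression, violence victimization, bullying", and two from school records, "Truancy, behavioral referrals". The text under Primary outcomes likewise covers both the survey and the school discipline data.

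Between group analyses (Power analyses) gives one detectable effect, d = .27 with power above .80, for 20 schools, 60 students per school and an ICC of .10. It reports earlier ICCs of .00 to .03. It states no alpha, no number of outcomes and no multiplicity allowance.

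**The concern.** Tukey's range procedure controls error over all pairwise comparisons of several group means on one outcome. The protocol assigns it a different job, control over several outcomes, in a design with a single pair of groups. A method described as conservative would then be no stricter than an unadjusted test.

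Bonferroni does adjust across outcomes, so the two methods can give opposite answers on the same measure, and the article gives neither precedence. If the Tukey result were relied on, the chance of at least one false positive among the primary measures would be well above 5%. If Bonferroni is relied on, the power for each measure is lower than the stated figure, which appears to rest on one test at .05.

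**Working it through.** **Inputs.** Two arms of 10 schools (Schools, Analysis). 60 students per school, so 600 per arm; d = .27; ICC .10 stated and .00 to .03 seen before (Between group analyses). Five measures in the primary row of Table 2, three of them from the survey. Alpha is not stated for this calculation; two-sided .05 is assumed.

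**1. The protocol's own figure.** Design effect DE = 1 + 59 × ICC; standard error of the difference in SD units = √(2 × DE/600); normal-approximation power = Φ(d/SE − z).

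- ICC .10: DE = 6.9, SE = √.0230 = .152, d/SE = 1.78, power = Φ(1.78 − 1.96) = .43. The effect detectable at 80% is .425, so d = .27 is not reproduced.
- ICC .03: DE = 2.77, SE = √.00923 = .0961, d/SE = 2.81, power = Φ(2.81 − 1.96) = .802. The effect detectable at 80% is .269.

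The stated .27 therefore matches one unadjusted two-sided .05 test at ICC .03.

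**2. Tukey with two groups.** With 20 − 2 = 18 df, the studentized-range critical value for two groups divided by √2 is 2.101. The two-sided .05 t value on 18 df is also 2.101, so the Tukey p-value is the unadjusted p-value.

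**3. Where the pair disagrees.** Bonferroni over k measures requires p < .05/k. With k = 5, any measure with .01 < p < .05 passes under Tukey and fails under Bonferroni.

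**4. Family-wise error if Tukey is relied on, five measures.** If independent: 1 − .95⁵ = .226. Simulation of five outcomes on 10 versus 10 school means gives .21, .18 and .13 at outcome correlations of .3, .5 and .8. Bonferroni gives .03 to .05 throughout.

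**5. Another meaning of Tukey.** A Tukey-type endpoint correction uses a per-test alpha of 1 − .95^(1/√5) = .0227. For five independent outcomes, family-wise error is then 1 − .95^√5 = .108.

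**6. Power at d = .27 after Bonferroni.** The t columns use a noncentral t on 18 df.

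| Alpha per test | ICC .03, normal | ICC .03, t | ICC .10, normal | ICC .10, t |
|---|---|---|---|---|
| .05 (one test) | .80 | .76 | .43 | .39 |
| .0167 (three survey measures) | .66 | .58 | .27 | .23 |
| .01 (five measures) | .59 | .49 | .21 | .17 |

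Each column should be read downwards. The multiplicity effect at ICC .03 is 80% to 59% (normal) or 76% to 49% (t). At ICC .10 it is 43% to 21% (normal).

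**The case against.** - **Precedence may be in the analysis plan.** A reader might infer that the trial has no defined success criterion. The document does not support that. Which adjusted p-value governs is commonly left to an analysis plan, which is not shown. If both adjustments must be met, Bonferroni governs and error is controlled. The inflated error is therefore conditional on relying on Tukey. What remains is that the article positively names a method that cannot do the job it is given.
- **Tukey may mean something else.** The endpoint correction in step 5 does act across outcomes, so the 23% would not apply to it. It still does not hold 5%.
- **Five co-primary tests are not declared.** The count comes from Table 2 and the Primary outcomes heading; the primary hypothesis speaks of violence reported by students. With only the three survey measures, power at ICC .03 is still 66% rather than 80%.
- **Independence is the unfavourable end.** Three measures come from the same survey of the same students, so 13% to 18% is more plausible than 23% if correlations are .5 to .8. A reader might also count 15 tests (five measures at three follow-ups) and reach 1 − .95¹⁵ = 54%. That treats repeated measurements as independent and assumes 15 separate confirmatory tests, whereas the stated primary strategy is mixed-effects models.
- **The ICC problem is separate.** It is tempting to say that multiplicity cuts power from 80% to 21% at ICC .10. The fall from 80% to 43% arises because d = .27 does not follow from that ICC.

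**Conclusion.** The point holds as a defect in the stated method. In a two-arm trial Tukey's range procedure equals the unadjusted test and gives no control across outcomes, and it conflicts with Bonferroni for any p between .05/k and .05. Relying on it for the five listed primary measures would give a family-wise error of about 23% (independent), 18% (correlation .5) or 13% (correlation .8); the endpoint correction would give about 11% (independent).

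The power statement shows no multiplicity allowance. This is inferred from its silence and from the match to one test at an assumed two-sided .05 with ICC .03. On that basis, power per measure falls from 80% to 59% with five measures, or to 66% with three (normal approximation).

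A reader might go further and infer that both school-record outcomes must lose primary status because the intervention changes how events are recorded. The Restorative justice section says "restorative justice provides a useful framework for alternatives to zero tolerance or traditional disciplinary actions for school violence". That gives a reason for care with behavioral referrals, which could fall because practice changed. It says nothing about truancy, and it does not make a new outcome hierarchy a required correction.

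**What to change.** Delete Tukey. State that Holm governs across the measures designated primary, and list those measures. Holm gives the same family-wise guarantee as Bonferroni and is never less powerful. Restate power at the adjusted alpha: .01 if all five measures stay primary, .0167 if only the three survey measures do. State the alpha and the ICC used, because the stated ICC of .10 and d = .27 do not agree even before adjustment.

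Optionally, the sponsor may name a single student-reported violence measure as primary, in line with the primary hypothesis, which would remove the adjustment at that level. This is a choice, not a required correction.

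The change is to wording and one recalculation, with no new data. Its cost is a less favourable power statement.

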### Power analyses

#### Between group analyses

Since the proposed intervention will be delivered within group (school) settings, data analyses examining treatment effects at the school level must account for the correlation among observations within school (i.e., intraclass correlations; ICC) due to shared factors within a school setting such as school selection factors (e.g., school attendance boundaries, family choice), similarities in treatment experiences (e.g., staff factors, resource factors), and within-school influences (e.g., common experiences with other students, cultural norms). Previous analyses of measures to be used in this study indicate small ICCs within schools for our outcome variables of interest (range: .00 to .03). If an ICC greater than zero is ignored, the outcome variance due to between-school differences (which can be large) is mixed with outcome variance due to between-participants variability within schools (which can be small because of the correlation). This can lead to large standard deviations, larger *p* values, and false-negative results (Chuang, Hripcsak, & Heitjan, 2002; Murray, Phillips, Bimbaum, & Lytle, 2001). Thus, our analytic strategy described below takes the ICC into account. Assuming 20 schools, 60 students per school, and a modest within-cluster correlation coefficient (ρ = .10), we will be able to detect standardized effect sizes at the school level of *d* = .27, representing a medium effect size, with probability (β > .80). Thus, our design will include 20 schools over the course of 2 years of the study period. The lagged implementation, however, limits across school comparisons (i.e., treatment vs control schools) until year three.

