#### Student eligibility and recruitment

There are 21 public school districts and 13 academies (charter schools) serving over 67,000 students in the GISD. Recruitment efforts will begin with presentations to the superintendents of the schools and academies. This will be followed up by similar presentations and briefings to school building principals and/or their designees (dean of students, academic services, teachers). The briefings explain the goals of the research project, the benefits to participating schools, anticipated intervention and research activities, eligibility, and similar issues. Eligibility includes having at least two grades between grades 4–6 and having a student population with 50% or higher free or reduced school lunch eligibility, being involved in MIBLISI (Michigan’s Integrated Behavior and Learning Support Initiative) and PBIS (Positive Behavioral Interventions & Supports) and being committed to the project. Across Genesee County, there are currently an average of 180 4th–6th graders in each school resulting in a maximum sample size of 3600 students over the course of the study (using a 66% consent/retention rate).

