#### Individual analyses

At the individual level, we will examine the hypothesized pathways using structural equation models while controlling for dependency due to school attended as noted above. Across Genesee County, there are an average of 180 4th–6th Graders in Flint schools resulting in a maximum sample size of 3600 students over the course of the study (we use a 33% consent/retention rate for calculations). Using the SEM power calculations suggested by MacCallum, Browne, and Sugawara (1996), we will have ample statistical power in SEM analyses for even our most complex models with 100 degrees of freedom (*df*). Power is based on the probability of rejecting the hypothesis of not a close fit with the data when the true model fit is excellent (the most stringent test). Our power with the 1200 (600 per condition) students is over .80. Notably, MacCallum et al. (1996)^.^ show that power of .80 is achievable with alpha = .05 and *df* of 100 with a sample as small as 178 for test of not-close fit.

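### The stated power does not follow from its inputs: with 20 schools, 60 students per school and ρ = .10 the detectable effect is about d = .42 to .45, not .27, and power for .27 is about 40%

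*Protocol article*

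**What the plan says.** Under Power analyses, Between group analyses, the Protocol article reports that earlier data gave "small ICCs within schools for our outcome variables of interest (range: .00 to .03"). It then sets out the inputs of the calculation: "Assuming 20 schools, 60 students per school, and a modest within-cluster correlation coefficient (ρ = .10), we will be able to detect". The answer it prints is a d of .27, which it describes as "representing a medium effect size, with probability (β > .80"). The next sentence draws the choice of 20 schools from this result. The Schools section fixes the allocation, "for a total of 10 intervention and 10 control schools". No α, sidedness, covariate gain or repeated-measures gain is given for this calculation.

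The figure of 60 students per school comes from an average of 180 eligible students per school and a consent/retention rate, and the article gives two rates. Student eligibility and recruitment has "resulting in a maximum sample size of 3600 students over the course of the study (using a 66% consent/retention rate"). Individual analyses has the same maximum of 3600 but adds "we use a 33% consent/retention rate for calculations", and goes on: "Our power with the 1200 (600 per condition) students is over .80".

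**The concern.** A ρ of .10 is more than three times the largest ICC the article reports, so it reads as a deliberate safety margin: the trial would keep over 80% power for d = .27 even if clustering were much stronger than seen before. A cluster trial with only 10 schools per arm is very sensitive to ρ, and d = .27 looks far too small for that margin.

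This is the only power statement for the comparison between arms; the one under Individual analyses concerns the fit of structural equation models. If it is wrong, the stated basis for 20 schools is wrong, and a null result could be read as evidence against an effect of .27 that the trial had less than an even chance of detecting under the printed scenario.

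**Working it through.** **Inputs.** J = 20 schools, m = 60 students per school, ρ = .10, d = .27, power above .80 (Between group analyses); 10 schools per arm (Schools); ICC range .00 to .03 (Between group analyses). Two-sided α = .05 is an assumption, because the article gives α = .05 only for the structural equation models.

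**Formulas.** For a difference in means in units of the total SD:

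- Design effect = 1 + (m − 1)ρ
- SE(d) = √(4[ρ + (1 − ρ)/m]/J)
- Detectable d at 80% power = (1.960 + 0.842) × SE = 2.802 × SE (normal), or (2.101 + 0.862) × SE = 2.963 × SE (t on J − 2 = 18 df)

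**The plan's figure.** It is reproduced at ρ = .03, not at ρ = .10. At ρ = .03, SE = √(4[.03 + .97/60]/20) = .0961 and the detectable d is 2.802 × .0961 = .269. Power for .27 is then 80.2% (normal). On 18 df the values are .285 and 75.7%.

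**The stated inputs.** At ρ = .10:

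- Design effect = 1 + 59 × .10 = 6.9; effective sample = 1200/6.9 = 174
- SE = √(4[.10 + .90/60]/20) = √.023 = .1517
- Detectable d = 2.802 × .1517 = .425 (normal); 2.963 × .1517 = .449 (t, 18 df)
- Power for d = .27: 42.9% (normal); 39.2% (t, 18 df)

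| ρ | Design effect | Detectable d, normal / t18 | Power for .27, normal / t18 |
|---|---|---|---|
| .00 | 1.00 | .162 / .171 | 99.7% / 99.3% |
| .01 | 1.59 | .204 / .216 | 96.0% / 93.9% |
| .02 | 2.18 | .239 / .253 | 88.6% / 85.0% |
| .03 | 2.77 | .269 / .285 | 80.2% / 75.7% |
| .10 | 6.90 | .425 / .449 | 42.9% / 39.2% |

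**Could an unstated choice give .27 at ρ = .10?** (normal / t)

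- One-sided α = .05: .377 / .392. One-sided α = .10: .322 / .330.
- 119 students per school (66% of 180): .411 (normal). All 180: .406 / .429.
- Unlimited students per school: 2.802 × √(4 × .10/20) = .396; 2.963 × .1414 = .419.
- Effect in school-level SD units: .425/√.115 = 1.25 (SD of school means) or .425/√.10 = 1.34 (between-school SD), further away.
- 20 schools per arm: two-sided .300 / .308, one-sided .267 / .272. Only the one-sided version comes to .27, and it contradicts the 10 + 10 allocation.
- Covariates: the variance term must fall from .115 to (.27/2.802)² × 20/4 = .0464. That means removing 1 − .0464/.115 = 60% of the variance at both levels, or (.115 − .0464)/.10 = 69% of the between-school variance with student-level variance unadjusted (64% and 73% by the t calculation).
- Number of schools needed for .27 at ρ = .10 with 60 students each: 4 × .115 × (2.802/.27)² = 49.5, so 50 (52 by the t calculation).

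**Consent/retention.** 20 × 180 = 3600 is every eligible student, with no loss. Applying 66% gives 2376; applying 33% gives 1188, or 59.4 per school. Only 33% agrees with the 60 per school and the 1200 in the power sections.

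**The case against.** The strongest reply is that the check uses one time point without adjustment, while the planned analysis is longitudinal, with four measurement occasions, linked student data and mixed-effects models. Baseline adjustment could recover much of the loss. Suppose, purely as an assumption, that autocorrelation is .8 between schools and .5 between students. The correlation of school means is then (.8 × .10 + .5 × .90/60)/.115 = .0875/.115 = .76, about 42% of the variance remains, and the detectable d at ρ = .10 falls to about .276 (normal) or .29 (t, 17 df). So the floor of .396 applies to the unadjusted comparison only. This shows what the sponsor could have argued. The power statement claims no such gain and gives no correlation to support one, and even these favourable values stop just short of .27.

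Three further points have some weight. That d came from ρ = .03 is an inference, and it fits only under the normal approximation. If the true ICC lies in the reported range, 20 schools is roughly adequate for d = .27. The article also commits to reporting effect sizes alongside tests, which limits the scope for misreading a null result. None of these makes ρ = .10 and d = .27 compatible.

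The side issues are minor. Writing power as β is a notation slip. Whether .27 is a medium effect depends on a convention the article does not state. The conflict between 66% and 33% hardly moves the result (.425 to .411 at ρ = .10).

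**Conclusion.** The power statement is wrong as written. On its own inputs the trial can detect d of about .42 to .45 rather than .27, and power for .27 is 39% to 43% rather than above 80%. This assumes two-sided α = .05, 10 schools per arm and an unadjusted comparison of means; no plausible change of α or sidedness, and no number of students per school, brings it to .27. The multiplicity adjustments planned in the Analysis section could only lower power further.

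This does not make the trial futile. At an ICC of .03 power for .27 is 76% to 80%, and it is higher below that. What fails is the claimed protection at ρ = .10, and with it the stated justification for 20 schools. The most likely explanation is a ρ and a d taken from different scenarios, but the correction is needed whatever the cause. The two consent/retention rates are a separate, smaller contradiction in the same chain of inputs.

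**What to change.** Replace the power statement with one that pairs each ρ with its own d, for example: with 20 schools (10 per arm), 60 analysed students per school, two-sided α = .05 and 18 df, the detectable effect at 80% power is d = .285 at ρ = .03 and d = .45 at ρ = .10. The sponsor must confirm α and sidedness, since neither is stated for this calculation. If a gain from baseline adjustment or repeated measures is intended, state its size and source and recompute d.

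Write power as 1 − β. Drop the word medium for .27, or call it small and name the convention used.

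Use one consent/retention rate in Student eligibility and recruitment and in Individual analyses. Give 3600 as the eligible number, and 1188 (33%) or 2376 (66%) as the number expected for analysis.

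The cost is wording, and a less favourable stated sensitivity. No extra schools are needed if the sponsor accepts the larger detectable effect at ρ = .10 or justifies an ICC of .03 or below. Keeping both ρ = .10 and d = .27 without an adjustment gain would take about 50 to 52 schools.
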